| Statistical Analysis:                   | 
As this study is a feasibility study, this study is not powered to achieve statistical significance. Rather we are aiming to understand if we can
 
 
a) recruit men and women of South Asian origin to an intensive weight management intervention
 
b) if the intervention is acceptable to the South Asian population
 
c) if individuals of South Asian origin can lose weight and achieve diabetes remission with the intervention
 
d) how the programme can be improved for use in a larger randomised controlled trial
 
e) define the mechanisms behind Type 2 diabetes remission in the South Asian population
 
                                                                                                                                                                                                                                                                                                                                                                                                                                                                                                                                                                               |

|  |  |
|--|--|
|  |  |
|--|--|

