## **6. STATISTICS AND DATA ANALYSIS**

The main objective of the study is to investigate if Counterweight Plus is acceptable to individuals of South Asian origins. This study is not powered to achieve a primary outcome, rather to investigate if it is possible to recruit, retain and achieve remission from diabetes in the South Asian population. Data will be collected on paper-based forms and entered into a secure SPSS file for analysis. Drug intolerance, diet intolerance or poor-compliance will be recorded. Trial documentation and data will be retained for at least 5 years.

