## **6.1 Sample size**

We aim to recruit 25 participants to the study. This figure has been chosen as this will give us enough information to assess the feasibility and acceptability of the programme to this population. We anticipate a failure to complete rate of about 25% (this may be greater at specific timepoints due to the COVID-19 pandemic). With 20 participants in a randomized comparison, the study can estimate the change in weight with a margin of error of 2.8kg assuming a standard deviation weight change over 3 months of 6kg. e.g., for an average observed weight change of 8kg (SD 6) we can estimate with 95% confidence that in the population the true weight change would lie between 5.1 and 10.7kg.

The proportion achieving remission in the combined intervention and delayed intervention groups (n=20) will be compared to the proportion achieving diabetes remission in the external DIADEM-1 trial control group (Taheri et al, Lancet Diabetes and Endocrinol, 2020) (12%; 95%CI 5%, 21%). Therefore assuming 12% remission in a usual care group (based on DIADEM), using a one sample proportion test, with 20 participants there will be 83% power to detect a significant difference if 30% of participants (n=6) or more achieve remission.

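### The 83% power stated for the remission comparison does not follow from its own inputs: with 20 participants and 12% versus 30%, the exact test gives 58% or 39%, and no 5% version checked exceeds 80%

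*Protocol*

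**What the plan says.** Protocol section 6.1 sets a recruitment target of 25 and justifies it by the information needed on feasibility and acceptability. It then adds a comparison on remission, with these elements:

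- The estimate is "The proportion achieving remission in the combined intervention and delayed intervention groups (n=20").
- The reference value comes from "assuming 12% remission in a usual care group (based on DIADEM"), an external trial's control group.
- The comparison is made "using a one sample proportion test".
- The claim is that "with 20 participants there will be 83% power to detect a significant difference if 30% of participants (n=6) or more achieve remission".

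The section gives no significance level, does not say whether the test is one- or two-sided, and does not say whether it is exact or a normal approximation. On attrition it says "We anticipate a failure to complete rate of about 25"%, possibly more at some timepoints because of the pandemic.

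Elsewhere the protocol makes no claim to power. The synopsis (Statistical Analysis) says "this study is not powered to achieve statistical significance", and section 6 says "This study is not powered to achieve a primary outcome".

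**The concern.** A one-sample test with 20 participants has limited power to separate 12% from 30%, because the expected counts are only 2.4 and 6 remissions. A claim of 83% therefore looks too high, and it can be checked from the inputs given.

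The wording also runs two things together. The phrase "if 30% of participants (n=6) or more achieve remission" can mean a true remission rate of 30% or an observed count of 6 out of 20. Power is defined only at an assumed true rate. An observed count is either significant or not.

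The figure matters because these results are meant to inform a larger trial. Someone who accepts 83% will put the chance of missing a true 30% remission rate at 17%. Under the exact test with the 6-or-more rule it is about 42% (1 − 0.584).

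**Working it through.** **Inputs (Protocol section 6.1):** n = 20; null rate p0 = 0.12, held fixed; alternative rate p1 = 0.30; one-sample proportion test. Alpha and sidedness are not stated, so 5% is assumed and both one- and two-sided versions are shown.

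**The plan's own figure:** 83%. It was not reproduced by any calculation below.

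**Exact binomial test.** Upper-tail probabilities for X remissions among 20:

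| Reject at | P(X ≥ k) at 12% | Power, P(X ≥ k) at 30% |
|---|---|---|
| 5 or more | 0.083 | 76.2% |
| 6 or more | 0.026 | 58.4% |
| 7 or more | 0.007 | 39.2% |

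- One-sided 5%: 5 or more is too liberal (0.083), so the cutoff is 6. Power is 58.4%.
- 2.5% per tail: 6 or more is just too liberal (0.026), so the cutoff is 7. Power is 39.2%.
- Two-sided 5% by the minimum-likelihood method: zero remissions has probability 0.88^20 = 0.078 under the null, more than the 0.019 for exactly 6, so the lower tail adds nothing. The cutoff is 6 and power is 58.4%.

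**Normal approximations.** The difference is d = 0.30 − 0.12 = 0.18.

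SE0 = √(0.12 × 0.88 / 20) = 0.0727 and SE1 = √(0.30 × 0.70 / 20) = 0.1025.

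z = 1.645 (one-sided 5%) or 1.960 (two-sided 5%). Φ is the standard normal distribution function.

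| Version | Formula | One-sided 5% | Two-sided 5% |
|---|---|---|---|
| Score | Φ[(d − z·SE0)/SE1] | Φ(0.590) = 72.2% | Φ(0.367) = 64.3% |
| Score, continuity-corrected | Φ[(d − z·SE0 − 1/(2n))/SE1] | Φ(0.346) = 63.5% | Φ(0.123) = 54.9% |
| Arcsine | Φ[2(asin√p1 − asin√p0)√n − z] | Φ(0.376) = 64.6% | Φ(0.061) = 52.4% |
| Wald | Φ[d/SE1 − z] | Φ(0.112) = 54.4% | Φ(−0.203) = 41.9% |
| Null variance only (shortcut) | Φ[d/SE0 − z] | Φ(0.832) = 79.7% | Φ(0.517) = 69.7% |

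**The two most generous 5% variants:**

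- The null-variance shortcut, one-sided, gives 79.7%. It ignores the larger variance at 30%. Its normal deviate happens to be 0.832, but whether that explains the printed 83% cannot be known, and nothing here depends on it.
- The one-sided score test applied to actual counts rejects at 5, because (0.25 − 0.12)/0.0727 = 1.79 exceeds 1.645. Its power is 76.2%, but its true type I error is 8.3%.

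**What would be needed for about 83%:**

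- *A looser alpha.* At one-sided 10% the score formula gives 80.2% and the null-variance shortcut 88.4%. The protocol states no such level.
- *A higher true rate.* With n = 20 and the 6-or-more rule, P(X ≥ 6) is 80.9% at a true rate of 37% and 83.3% at 38%. With the 7-or-more rule it is 82.8% at 43%.

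**Sensitivity to n.** 25 × 0.75 = 18.75. With 19 assessed, the exact one-sided 5% cutoff is still 6 (P(X ≥ 6) at 12% = 0.020) and power at 30% is 52.6%.

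**The case against.** The strongest objection is that this is a feasibility study which says, in the synopsis and in section 6, that it is not powered. The 25 was not derived from the remission calculation, so correcting the figure changes no sample size, endpoint or analysis. That stands, and it limits the severity. It does not make the number right.

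A second objection is that, with no alpha, sidedness or test version given, 58% is no more the protocol's figure than 39% or 72%. That also stands. The finding is that 83% is not reached at 5%; 58% is conditional on an exact test that rejects at 6.

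Some stronger readings are tempting but not supported:

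- *That 6 of 20 is bound to be significant.* It is under a one-sided 5% or minimum-likelihood two-sided exact test (p = 0.026). It is not under an equal-tailed two-sided 5% test, where the doubled p is 0.052.
- *That the analysed number must be 19.* The attrition figure is approximate, and section 3.5 plans to use end-of-study diabetes status for people who leave the programme. Failing to complete need not mean loss from this comparison.
- *That the synopsis and section 6 need correcting.* They disclaim power, and a lower figure in section 6.1 agrees with them better than 83% does.
- *That this is the only formal test, or that a non-significant result would be held against the programme.* Section 6.2 leaves the analyses to a SAP that is not at hand, and no text sets such a decision rule.

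**Conclusion.** The 83% is wrong as written. On the protocol's inputs, power at a true remission rate of 30% is 58% (exact, rejecting at 6 or more) or 39% (exact, rejecting at 7 or more). It is about 42% to 72% by the usual normal approximations, and 76% to 80% by the loosest 5% variants. The overstatement is about 25 percentage points against the exact test at the count that section 6.1 itself names, and at least 3 points against the most generous version.

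This rests on a 5% significance level, which is an assumption, and on treating the external 12% as known, as the protocol does. If a larger alpha was intended, it needs to be stated.

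A reader might infer that the trial is too small and must recruit more. The documents do not support that, because the target of 25 rests on feasibility and acceptability. This is a should-fix correction to a supporting figure, not a flaw in the design.

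**What to change.** In section 6.1, state the alpha, the sidedness and the version of the test, in agreement with the SAP, and replace 83% with the power that matches. Say that 30% is an assumed true rate, and give the rejection count separately. Suggested wording, to be cut to whichever test is chosen:

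> Exact binomial test against 12% with 20 assessed participants. At one-sided 5% the test rejects at 6 or more remissions; power is 58% if the true rate is 30% and 83% if it is 38%. With 2.5% per tail it rejects at 7 or more; power is 39% if the true rate is 30%.

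Optionally add 53% for 19 assessed participants under the 6-or-more rule, as a sensitivity figure. The synopsis and section 6 can stay as they are.

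The cost is a few lines of text and a less favourable number. No patients, visits or procedures are added.

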## **6.2 Management and delivery**

The co-investigators will manage and analyse trial data. All statistical analyses will be conducted according to a pre-specified Statistical Analysis Plan.

## **7.0 STUDY CLOSURE / DEFINITION OF END OF STUDY**

The trial will last for 13 months in total. All participants will have completed 6 months follow-up by the end of the first year. This will give 6months to recruit all participants to the study.

## **8. Data Handling**

The study will follow a randomised controlled design. A blinded envelope system will be used for treatment allocation. The randomisation sequence will be produced by an independent researcher from the University of Glasgow using an online number generation tool. Envelopes will be prepared by the same researcher who will play no part in recruitment, treatment allocation or delivery of the intervention.

### **8.1 Case Report Forms / Electronic Data Record**

Data will be entered into the practitioner workbook, then transferred into an SPSS data file. This will be stored securely on the University of Glasgow drive. Access will only be possible for the named applicants of this study and study sponsors for audit purposes.

### **8.2 Record Retention**

Data will be held for a minimum of 5 years

## **9. STUDY MONITORING/AUDITING**

This study research team will monitor recruitment to ensure the required numbers are recruited to the study in the time frame.

### **Adverse Event Monitoring**

Enquiry at each study visit will identify the occurrence of adverse, or events of interest and these will be recorded (**App F**). In the case of any serious adverse event occurring, the PIs of the study will be informed immediately, and these managed with guidance from the PIs. The study sponsor and REC will also be informed of any serious adverse events.

## **10. PROTOCOL AMENDMENTS**

Any change in the study protocol will require an amendment. This will be discussed with Sponsor and submitted to REC.

## **11. ETHICAL CONSIDERATIONS**

The study will be carried out in accordance with the World Medical Association Declaration of Helsinki (1964) and its revisions (Tokyo [1975], Venice [1983], Hong Kong [1989], South Africa [1996] and Edinburgh [2000]).

Favourable ethical opinion will be sought from an appropriate REC before patients are entered into this clinical trial. Patients will only be allowed to enter the study once either they have provided written informed consent. The PI will be responsible for updating the Ethics committee of any new information related to the study.

## **12. INSURANCE AND INDEMNITY**

The South Asian Diabetes Remission Feasibility Study is sponsored by NHS Greater Glasgow & Clyde. In this case the Sponsor will be responsible for negligent harm due to the management/conduct of the study through the Clinical Negligence and Other Risks Indemnity Scheme (CNORIS). Harm from the design of the study will be covered by the University of Glasgow's clinical trials insurance. The NHS has a duty of care to patients treated, whether or not the patient is taking part in a clinical trial, and the NHS remains liable for clinical negligence and other negligent harm to patients under its duty of care.

## **13. FUNDING**

### **FUNDER:**

Department of Human Nutrition, University of Glasgow  
Department of Metabolic Medicine, University of Glasgow

## **14. ANNUAL REPORTS**

Annual progress reports will be submitted as directed by the study sponsor.

## APPENDIX A: STANDby SCHEDULE OF ASSESSMENTS

| APPENDIX 1: STANDARD SCHEDULE OF ASSESSMENTS |                   |                              |          |          |          |          |           |           |                           |           |            |            |
|----------------------------------------------|-------------------|------------------------------|----------|----------|----------|----------|-----------|-----------|---------------------------|-----------|------------|------------|
| Appointment
Week                          | 0
0 (Baseline) | Total Diet Replacement Phase |          |          |          |          |           |           | Food Reintroduction Phase |           |            |            |
|                                              |                   | 1
0+1                     | 2
0+2 | 3
0+4 | 4
0+6 | 5
0+8 | 6
0+10 | 7
0+12 | 8
0+13                 | 9
0+15 | 10
0+17 | 11
0+19 |
| Study Procedure                              |                   |                              |          |          |          |          |           |           |                           |           |            |            |
| Review & discuss study participation         | √ a    |                              |          |          |          |          |           |           |                           |           |            |            |
| Review Inclusion/Exclusion Criteria          | √ a    |                              |          |          |          |          |           |           |                           |           |            |            |
| Obtain Informed Consent                      | √ a    |                              |          |          |          |          |           |           |                           |           |            |            |
| Height                                       | √ a    |                              |          |          |          |          |           |           |                           |           |            |            |
| Weight                                       | √                 | √                            | √        | √        | √        | √        | √         | √         | √                         | √         | √          | √          |
| Waist Circumference                          | √                 |                              |          |          |          |          |           | √         |                           |           |            | √          |
| Hip Circumference                            | √                 |                              |          |          |          |          |           |           |                           |           |            | √          |
| Blood Pressure                               | √                 | √                            | √        | √        | √        | √        | √         | √         | √                         | √         | √          | √          |
| Blood samples c                   | √                 |                              |          |          |          |          |           | √         |                           |           |            | √          |
| Capillary blood glucose                      |                   | √                            | √        | √        | √        | √        | √         | √         | √                         | √         | √          | √          |
| Repeat HbA1c                                 |                   |                              |          |          |          |          |           |           | √                         |           |            | √          |
| EQ-5D questionnaire                          | √                 |                              |          |          |          |          |           |           |                           |           |            | √          |
| Participant Expectation Questionnaire        | √ a    |                              |          |          |          |          |           |           |                           |           |            |            |
| Psychological Process Questionnaire          | √                 |                              | √        | √        | √        | √        | √         | √         | √                         | √         | √          | √          |
| MR Scanning c                     | √                 |                              |          |          |          |          |           |           |                           |           |            | √          |
| MR Measurements b                 | √                 |                              |          |          |          |          |           |           | √                         |           |            | √          |
| Body Composition Measurements b   | √                 |                              |          |          |          |          |           |           | √                         |           |            | √          |
| Appetite hormones b               | √                 |                              |          |          |          |          |           |           | √                         |           |            | √          |

a initial visit only

b optional measurements

c Control participants only – Bloods, MRI scan & optional measurements repeated at end of control period

## **Appendix B: Measurement of Metabolic Rate, appetite hormones and Body Composition**

### *Resting and non-resting metabolic rate and appetite hormone measurements*

Metabolic rate will be measured by indirect calorimetry in the fasted state and after breakfast by means of computerised open-circuit ventilated hood system (Quark RMR, Cosmed, Italy). For non-resting metabolic rate, the participant will undertake a low intensity walking test on a treadmill (Trackmaster Treadmills, Full Vision, Inc., Kansas, USA) during which intensity will be gradually increased from 2 km/h to 5 km/h. The whole test is expected to last no longer than 20 minutes. Blood samples will be taken before and after breakfast to measure gut appetite hormones (PYY, GLP1, CCK), leptin and insulin.

### *Anthropometric and Body Composition Measurements*

Height will be measured to the nearest 0.5 cm using a stadiometer (Seca, Leicester, UK). Body mass and body fatness will be measured using leg-to-leg bioelectrical impedance scales (TBF-300, TANITA, Cranela, UK) (Androutsos et al., 2015). Waist circumference will be measured using a non-elastic tape measure.

### *Adaptive reduction in thermogenesis*

Adaptive reduction in thermogenesis will be calculated as the differences between measured and predicted metabolic rate. As described above, measured values will be obtained by indirect calorimetry. Predicted values will be calculated using regression equations incorporating fat mass and fat free mass (as well as age and sex), and anthropometric measurements (height, weight).

Participants will attend the metabolic laboratory at the New Lister Building, Glasgow Royal Infirmary for the above measurements which will be carried out by trained and experienced research staff.

## Appendix C: Counterweight Plus Programme Appointment Planner

### APPOINTMENT PLANNER

| TOTAL DIET REPLACEMENT (APPOINTMENT 1)                                                                                                                                                                                                            |                                                                                                                                                                                                                                                                                                                                                                                                                                                                                                                                                                                                                                                                                                                                                                                                                                                                                                                                                                                                                                                                                                                                                                                                                                                                                                                                                                                                                                                                                                                                                                                                                                                                                                                                                                                                                                                                                                                                               |
|---------------------------------------------------------------------------------------------------------------------------------------------------------------------------------------------------------------------------------------------------|-----------------------------------------------------------------------------------------------------------------------------------------------------------------------------------------------------------------------------------------------------------------------------------------------------------------------------------------------------------------------------------------------------------------------------------------------------------------------------------------------------------------------------------------------------------------------------------------------------------------------------------------------------------------------------------------------------------------------------------------------------------------------------------------------------------------------------------------------------------------------------------------------------------------------------------------------------------------------------------------------------------------------------------------------------------------------------------------------------------------------------------------------------------------------------------------------------------------------------------------------------------------------------------------------------------------------------------------------------------------------------------------------------------------------------------------------------------------------------------------------------------------------------------------------------------------------------------------------------------------------------------------------------------------------------------------------------------------------------------------------------------------------------------------------------------------------------------------------------------------------------------------------------------------------------------------------|
| Resources                                                                                                                                                                                                                                         | Practitioner tasks and discussion points                                                                                                                                                                                                                                                                                                                                                                                                                                                                                                                                                                                                                                                                                                                                                                                                                                                                                                                                                                                                                                                                                                                                                                                                                                                                                                                                                                                                                                                                                                                                                                                                                                                                                                                                                                                                                                                                                                      |
| 
Provide the COUNTERWEIGHT PLUS Total Diet Replacement Folder:
 
Welcome to COUNTERWEIGHT PLUS
 
Weight Tracker
 
Getting Ready
 
Daily Living Diary
 
Managing Difficult Times
 
Total Diet Replacement Plan
 | 
Welcome to COUNTERWEIGHT PLUS
 
Discuss programme stages and support. Individual and Practitioner to sign the Promise
 
Weight Tracker
 
Measure and record weight and waist circumference on weight tracker and data collection system
 
Getting Ready
 
Discuss the following:
 
 
- advantages and disadvantages
 
- dealing with disadvantages
 
- weight history, previous weight loss attempts, weight loss expectations
 
- set initial 5% weight loss target, and advise on weekly weight loss target
 
- self monitoring of weight at home Total Diet Replacement Plan Discuss and plan for:
 
- a typical day's intake on 800+ Calories Plan including fluid intake
 
- preparing shakes and soups and important considerations
 
- possible side effects, causes and what actions to take, and other considerations. Prescribe fibre supplement as appropriate
 
 
Ensure a minimum of 1 weeks supply of shakes and soups is available - consider flavour preferences and use sachet table to calculate quantity of provision
 
Daily Living Diary
 
Discuss importance of diary keeping. Advise to keep diary for first 2-3 days of the Total Diet Replacement Plan. Highlight the value of recording side effects and bowel habits
 
Managing Difficult Times
 
Discuss the following:
 
 
- Stop, Think, Learn and Plan technique
 
- High risk situations and alternative activities
 
- Planned and unplanned time off the Total Diet Replacement Plan
 
- Written plan for planned time off
 
- Social support
 
 
Weight Tracker
 
Agree next appointment and record on tracker. Record Counterweight Practitioner name, contact telephone number and advise on best contact method
 |

| TOTAL DIET REPLACEMENT (APPOINTMENT 2)          |                                                                                                                                                                                                                                                                                                                                                                                                                                                                                                                                                                                                                                                                                                                                                                                                                                                                                                                                                                                                                                                                                                 |
|-------------------------------------------------|-------------------------------------------------------------------------------------------------------------------------------------------------------------------------------------------------------------------------------------------------------------------------------------------------------------------------------------------------------------------------------------------------------------------------------------------------------------------------------------------------------------------------------------------------------------------------------------------------------------------------------------------------------------------------------------------------------------------------------------------------------------------------------------------------------------------------------------------------------------------------------------------------------------------------------------------------------------------------------------------------------------------------------------------------------------------------------------------------|
| Resources                                       | Practitioner tasks and discussion points                                                                                                                                                                                                                                                                                                                                                                                                                                                                                                                                                                                                                                                                                                                                                                                                                                                                                                                                                                                                                                                        |
|                                                 | 
Weight Tracker
Measure and record weight on Weight Tracker and data collection system
 
Getting Ready
Review weight loss expectations, and targets. Amend target if necessary
 
Total Diet Replacement Plan
Discuss progress and compliance with Total Diet Replacement Plan
Review side effects, activity, tolerance to fibre supplement and bowel habits
Ensure 3 weeks shakes and soups available - consider flavour preferences and use sachet table to calculate provision
 
Daily Living Diary and Managing Difficult Times
Review use of sections for self monitoring and relapse prevention strategies
 
Weight Tracker
Agree next appointment and record on tracker. Highlight importance of weekly self weighing
                                                                                                                                                                                                                                                                            |
| TOTAL DIET REPLACEMENT (APPOINTMENTS 3,4,5,6,7) |                                                                                                                                                                                                                                                                                                                                                                                                                                                                                                                                                                                                                                                                                                                                                                                                                                                                                                                                                                                                                                                                                                 |
|                                                 | 
Weight Tracker
Measure and record weight on Weight Tracker and data collection system
 
At Appointment 7
- Calculate BMI and measure waist circumference
- If >15kg weight loss is not achieved continue on Total Diet Replacement Plan up to 20 weeks
- If weight loss > 15kg NOTE: Only 1 week between Appointment 7 and 8
 
Review Getting Ready
Review weight loss expectations, and targets. Amend target if necessary
 
Total Diet Replacement Plan
Discuss progress and compliance with Total Diet Replacement Plan
Review side effects, activity, tolerance to fibre supplement and bowel habits
Ensure supply of shakes and soups - consider flavour preferences and use sachet table to calculate provision
 
Managing Difficult Times and Daily Living Diary
Review use of sections for self monitoring and relapse prevention strategies
 
Weight Tracker
Agree next appointment and record on tracker. Highlight importance of weekly self weighing
 |

| FOOD REINTRODUCTION PLAN (APPOINTMENT 8)                                                                                                                                                                                                                                                                    |                                                                                                                                                                                                                                                                                                                                                                                                                                                                                                                                                                                                                                                                                                                                                                                                                                                                                                                                |
|-------------------------------------------------------------------------------------------------------------------------------------------------------------------------------------------------------------------------------------------------------------------------------------------------------------|--------------------------------------------------------------------------------------------------------------------------------------------------------------------------------------------------------------------------------------------------------------------------------------------------------------------------------------------------------------------------------------------------------------------------------------------------------------------------------------------------------------------------------------------------------------------------------------------------------------------------------------------------------------------------------------------------------------------------------------------------------------------------------------------------------------------------------------------------------------------------------------------------------------------------------|
